## Abstract

**Background:**

Total hip arthroplasty is a highly successful procedure for treating hip arthritis, improving patients’ pain, function, and quality of life (QoL). Scarce publications on total hip arthroplasty performance using Brazilian-manufactured materials report results comparable to those from other countries.

**Objective:**

The aim of this study is to compare the clinical, radiographic, functional, pain, and QoL outcomes of patients who underwent surgery with a national hybrid prosthesis (with femoral cementation) versus patients who underwent surgery with a national uncemented prosthesis.

**Methods:**

This study is a single-center, single-surgeon, single-approach, pragmatic, double-blinded, and prospective randomized trial. A total of 120 patients will be enrolled and randomly allocated in a 1:1 ratio to 2 groups: the hybrid group and the uncemented group. The incidence of complications (during and after surgery) and the restoration of normal anatomical parameters on postoperative radiographs will be assessed using radiographic parameters. Participants’ QoL, joint mobility, function, and satisfaction will be evaluated using the 12-Item Short Form Health Survey version 2 questionnaire, hip range of motion, the Harris Hip Score, and a numeric rating scale. Prosthesis survival will be analyzed using the annual revision surgery rate from 1 to 5 years, and up to 10 years.

**Results:**

The project did not receive external funding. Data collection began in October 2024 and is ongoing, with completion expected in December 2029. As of April 2025, 72 participants have been enrolled. Preliminary data analysis has been initiated and is ongoing. The first results are expected to be published in the first half of 2026.

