**Figure 1. F1:**
[figure not shown]
Flowchart of the study protocol. mHHS: modified Harris Hip Score; mo: months; SF-12: 12-Item Short Form Health Survey; wk: weeks; y: years; *: clinical evaluator; **: surgeon; ***: radiographic evaluator; ****: data curator (supervisor).

Standard digital anteroposterior pelvis radiographs with calibration spheres will be obtained. A clinical interview and thorough preoperative evaluation will be undertaken by a medical doctor (orthopedic surgery resident). Functional, pain, and QoL questionnaires will be administered at this point, and surgical appointments will be scheduled (Multimedia Appendix 1).

Patient assignment and preoperative evaluations will be conducted in monthly blocks of 12 patients for practical and logistic purposes. Random allocation of patients to each group, the HG and the UG, will be performed at this time using double blinding.

At this stage, the surgeon will be blinded to group allocation and clinical assessment and will perform surgical planning for both uncemented and hybrid procedures using Peekmed software (Peekmed Inc, Braga, Portugal). Peekmed is a highly sensitive tool currently in use that focuses on digital surgical planning to evaluate the accuracy of corrections and to reproduce patient-specific anatomy. Data from both surgical plans will be extracted by the same surgeon using a specially designed digital form (MultimediaAppendices 2  3). Reports of the surgical plans will be printed and kept until surgery; however, only the correct plan, as decided by the random group allocation, will be provided to the surgeon by the assistant researcher before surgery.

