### Secondary Outcomes

Secondary outcomes will include comparisons of QoL, joint mobility, function, satisfaction, and pain before and after the surgery, as well as radiographic parameters extracted from the immediate postoperative radiograph. The annual frequency of revision surgeries will be recorded.

QoL will be evaluated using 12-Item Short Form Health Survey version 2 questionnaire [21]. QoL is defined as an individual’s perception of their position in life in the context of the culture and value systems in which they live and about their goals, expectations, standards, and concerns [21]. The 12-Item Short Form Health Survey is an instrument for measuring QoL composed of 12 items that assess eight different dimensions of influence on QoL, considering the individual’s perception of aspects of their health in the last 4 weeks [21]. Each dimension’s score is summed up, and the final score can be between 0 and 100; the higher the score, the better the QoL [22].

Participant satisfaction assessment will be measured using a 10-point numerical rating scale ranging from 1 (very dissatisfied) to 10 (completely satisfied) [23].

Other aspects of health, such as pain, will be evaluated through the Visual Analog Scale. The Visual Analog Scale provides a simple and efficient measure of pain intensity and is used when a fast pain index that can be assigned to a numerical value is needed [24].

Radiographic parameters will include the ability to restore anatomical normality parameters on postoperative radiographs according to the surgical plan (namely the limb length discrepancy, the horizontal off-set of the hip, difference between the back of the prosthesis and the tip of the trochanter, inclination of the acetabular component, and the difference between offset obtained to the normal side) all of this using the Peekmed surgical planning software.

The annual frequency of revision surgery will be observed starting from 1 year after surgery and annually until 5 years, and up to 10 years.

All questionnaires will be administered by examiners blinded to the surgical procedure. Questionnaires will be completed using digital devices (computer or tablet).

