## Results

The study started in October 2024. As of April 2025, 72 participants have been enrolled and operated on, corresponding to 60% of the target population. As the study timeline is being maintained, the first data analysis of the complete population was performed in November 2025, reporting population characteristics, radiographic and intraoperative findings, and early complications. The first results are expected to be published in the first half of 2026.

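### With data collection ending in December 2029, no patient can exceed 5.25 years and many cannot reach 5, yet revision results are promised to 5 and up to 10 years

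*Protocol article*

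**What the plan says.** The follow-up horizon for revision is given twice. The Methods paragraph of the abstract states: "Prosthesis survival will be analyzed using the annual revision surgery rate from 1 to 5 years, and up to 10 years". The Secondary Outcomes section says that the yearly frequency of revision surgery "will be observed starting from 1 year after surgery and annually until 5 years, and up to 10 years", so the clock runs from each patient's own operation.

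The calendar is given separately. The Results paragraph of the abstract states: "Data collection began in October 2024 and is ongoing, with completion expected in December 2029". The main Results section agrees on the start ("The study started in October 2024") and reports progress: "As of April 2025, 72 participants have been enrolled and operated on, corresponding to 60% of the target population". The same section places a first analysis of the whole study population in November 2025, which implies that all 120 had been operated on by then. On pace, the section on recruitment and preoperative assessment says: "Patient assignment and preoperative evaluations will be conducted in monthly blocks of 12 patients for practical and logistic purposes".

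The article mentions no extension phase, registry linkage or later contact after December 2029.

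**The concern.** The closing date lies about five years after the first operation, but the promised horizon runs from every patient's operation, including the last. The two can agree only if the horizon is shortened or the closing date is moved.

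Durability is part of the trial's question. The Introduction says that doubts persist about the durability of Brazilian-made implants and lists the need for revision among the outcomes to be compared. The Conclusion hopes to identify a preferred construct. A reader would take from the article that 10-year revision data are coming, when the stated calendar cannot produce them. If collection does close in December 2029, 5-year status will also be unknown for a large part of the sample. A 5-year proportion that used all 120 as its denominator would then count hips not yet observed for 5 years as unrevised, and would understate revision.

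**Working it through.** **Inputs**
- Start: October 2024 (abstract Results; main Results).
- End of data collection: December 2029 (abstract Results).
- Sample size: 120, allocated 1:1 (abstract Methods).
- Operated on as of April 2025: 72 (main Results).
- Planned pace: 12 per month (recruitment and preoperative assessment).
- Whole population available by November 2025 (main Results, by implication).

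**Check of the article's own figure.** 72 / 120 = 60%, as stated. That leaves 120 − 72 = 48 patients still to be operated on.

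**Step 1: longest possible follow-up.** Closing date minus earliest possible surgery: 1 October 2024 to 31 December 2029 = 5.25 years. With the least favourable days in the same months (31 October 2024 to 1 December 2029) it is 5.08 years. Nobody can contribute to years 6 to 10. This step needs no assumption about accrual.

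**Step 2: who can reach 5 years.** Five years by 31 December 2029 requires surgery by 31 December 2024.
- *Without any accrual assumption:* the 48 patients not yet operated on as of April 2025 cannot qualify. 48 / 120 = 40% is the minimum that must miss 5 years.
- *Even accrual at the planned pace (assumption):* 3 months × 12 = 36 operated on by the end of December 2024. 36 / 120 = 30% can reach 5 years and 84 / 120 = 70% cannot.
- *Even accrual at the observed pace (assumption):* 72 / 7 months = 10.3 per month, and 3 × 10.3 ≈ 31. 31 / 120 = 26% can reach 5 years and 89 / 120 = 74% cannot.
- *Less favourable days within the stated months, accrual still even:* the share that cannot reach 5 years rises to about 90%.

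**Step 3: what everyone can have.** If the last surgery was on 31 July 2025, follow-up to 31 December 2029 is 4.42 years. If it was on 1 November 2025, follow-up is 4.16 years. Complete follow-up is therefore about 4 years.

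**Step 4: dates that would match the promise.** Last surgery between about July and November 2025, plus 5 years, gives about July to November 2030. Plus 10 years gives about July to November 2035. The first patient would reach 10 years in October 2034.

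**The case against.** The strongest reply is that the wording on 10 years may refer to a later extension, and that an article condenses a fuller protocol. A condensed article may well leave out the details of an extension. The difficulty here is that two positive statements disagree: one closing date for data collection, and one horizon that runs past it. An extension would explain the 10-year phrase, but not the yearly series to 5 years, which also overruns the closing date for at least 40% of patients.

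Several stronger readings are tempting, and the article does not support them.

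- *That no 5-year result is possible.* Only complete 5-year observation fails. An estimate that censors patients at last contact remains possible, although under even accrual only about 31 to 36 patients could be observed that far. Yearly results for years 1 to 4 can cover all patients if surgery finished by November 2025.
- *That 70% is a fact.* The article does not say how many were operated on by December 2024. The figure depends on even accrual; only the 40% minimum follows from the stated counts.
- *That revisions in the first year are left out,* because observation is said to start at 1 year. The Primary Outcomes section has a form completed at any readmission or further surgery, and the Statistical Analysis section analyses reoperations at 48 weeks. The natural reading is that the first yearly count is taken at 1 year.
- *That 5-year revision will be compared as a crude proportion by chi-square.* The Statistical Analysis section names Fisher and chi-square tests for dichotomous variables in general. It does not specify the denominator or the method for 5-year revision, and that detail may properly sit in an analysis plan that is not shown.

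**Conclusion.** The concern holds as an inconsistency between the calendar and the follow-up horizon. The absence of any data beyond 5.25 years follows from the stated months alone. So does the finding that at least 40% of patients cannot reach 5 years, given the stated count of 72. The larger share of about 70% to 74% rests on even accrual at 10.3 to 12 per month. The statement that everyone can have about 4 years rests on surgery having finished by November 2025, which the article implies but does not say outright.

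The point should be fixed, but its reach is limited. Revision over the years is a secondary outcome. The primary outcomes are analysed at 48 weeks and the sample size is built on the Harris Hip Score; neither is affected.

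**What to change.** Reconcile the closing date and the horizon in one of two ways, and use the same wording in the abstract, the Secondary Outcomes section and the Results.

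(a) Move the end of data collection to 5 years after the last surgery, about late 2030, and describe any 10-year contact as a separate, defined extension. The cost is follow-up contact beyond the present closing date.

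(b) Keep December 2029, state that complete follow-up is about 4 years, and drop the 10-year claim. The cost is a less favourable stated horizon.

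If December 2029 is kept and a 5-year revision figure is still reported, give it as a time-to-event estimate from the date of surgery, censored at last contact, with the numbers at risk in each arm. Hips not yet observed for 5 years are then not counted as unrevised, and the reader can see how few patients support the estimate. This needs only analysis wording and the dates of surgery and last contact.

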**Conclusions:**

This study is a pragmatic clinical trial that uses blinding to evaluate national implants for both hybrid and uncemented hip arthroplasty. Successful completion of this study may provide clinical evidence on the performance of national implants and identify a preferred implant construct (hybrid or uncemented), if any, for hip replacement in Brazil.

## Introduction

Total hip arthroplasty (THA) is a highly successful procedure for treating hip arthritis, improving patients’ pain, function, and quality of life (QoL) [1,2]. However, THA is still vulnerable to complications such as fractures, loosening, infection, as well as other biological issues [3]. Because patients who undergo THA face the risk of cumbersome and costly revision procedures, the life expectancy and durability of the implant are important issues [3]. Different surgical techniques and implants, such as cemented and uncemented stems, are used to perform THA [4]. However, despite the good results of this procedure, no single surgical technique or type of implant has been proven superior for all patients [4].

To date, considerable controversy persists regarding the best type of surgical implant. While in North America, there is a preference for noncemented implants [4], this is mainly based on the findings of a 17-year follow-up randomized controlled trial (RCT) published by Corten et al [5] in 2011. In other countries, especially in Europe, the preference for cemented femoral implants has been maintained. The latter is supported by at least 6 RCTs that show no differences between these types of implants [4], as well as reports of a greater incidence of surgical complications with uncemented implants, especially in older patients [6].

Worldwide, the increasing use of uncemented implants has been described as the “paradox of the decline of cemented implants” [7]. In fact, Troelsen et al [8] in 2013 analyzed 7 national registries, including Australia, Canada, England, Denmark, New Zealand, Norway, and Sweden, in which the use of uncemented prostheses showed a steady increase in the use of this kind of prostheses [8]. Recent studies have highlighted an increased “cementless” trend in some countries between 2010 and 2020; however, this trend appeared to be reversing in others, such as England and Wales, Australia, New Zealand, and Finland [9]. Those authors agree that survival was significantly better for cemented prostheses in all registers in people aged older than 70 to 75 years [8,9]. For other age groups, survival was better for cemented prostheses or equivalent, except in the Australian register. Using another approach to the problem, a meta-analysis including 27 studies conducted by Phedy et al [10] reported very similar results, showing equivalence of both types of implants in the younger patients and superiority of cemented fixation in older patients.

While most RCTs in this area of research have traditionally focused on implant survival and revision rates [4], patient-centered outcomes, QoL, and early complications have become a current hot topic. Hybrid THA yields similar short- to mid-term patient-reported outcome measures (Harris Hip Score [HHS], WOMAC, EQ-5D) compared with cemented and uncemented constructs. A 2025 systematic review of 357,748 THAs found no difference in patient-reported outcome measures between hybrid and cemented THA and no clear advantage of uncemented constructs [11]. However, the incidence of periprosthetic fracture was reported to be significantly higher with uncemented stems, especially in older adults. Moreover, a slightly higher incidence of dislocations was also reported for uncemented stems [12]. Regarding pain, direct elective THA comparisons are limited, but evidence consistently shows more early pain and slower recovery with uncemented femoral fixation due to press-fit stem insertion forces. A meta-analysis of RCTs in THA showed better short-term pain scores with cemented fixation [13]. Additionally, a large National Health Service cost-effectiveness analysis (n≈300,000) found higher postoperative EQ-5D scores with hybrid THA (0.81 vs 0.80 for uncemented), and for most patient groups, hybrid prostheses were found to be the most cost-effective [14].

Few publications on THA performance using Brazilian-manufactured materials have reported results comparable to those from other countries; however, the level of evidence and sample sizes of these studies are limited [15-17]. Additionally, early failures of previous national models, commonly used in Brazil until the 1990s, became the reason for persistent questioning about the safety and durability of Brazilian-made implants [18]. To date, no level 1 study evaluating the performance of such implants in Brazil has been identified.

This study aims to compare the clinical outcomes (function, pain, complications, QoL, and need for revisions) and radiographic outcomes of patients treated with a national hybrid prosthesis (with femoral cementation and uncemented acetabular cup) versus those receiving national uncemented prostheses of the same brand.

## Methods

### Study Design and Setting

This study was written according to the Standard Protocol Items: Recommendations for Interventional Trials (SPIRIT) guidelines (Checklist 1) for protocols of randomized clinical trials. The proposal is a single-center, single-surgeon, single-approach, pragmatic, double-blinded, prospective randomized trial to analyze the differences between uncemented hip replacement and the hybrid (femoral cemented) hip replacement.

Two different types of hip implants will be used for comparison: the Maxima Cemented Vincula Stem (Víncula, Rio Claro, SP, Brazil) and the Taper Uncemented Primary Stem (Víncula, Rio Claro, SP, Brazil). Patients and evaluators will be blinded to group allocation: the hybrid group (HG) and the uncemented group (UG). A total of 120 patients will be enrolled in this study and randomly allocated to each group in a 1:1 ratio.

### Recruitment and Preoperative Assessment

All the patients ascribed to a waiting list for hip arthroplasty in a hip reconstruction ambulatory of a tertiary teaching hospital in Juiz de Fora-MG, in southeast Brazil (Hospital e Maternidade Therezinha de Jesus) will form the recruitment base for this study. This study was approved by an institutional review board, registered in the Brazilian Registry of Clinical Trials (RBR-263nf22), and assigned the Universal Trial Number U1111-1313-6912. All eligible patients will be informed verbally about the study and its objectives and will be invited to participate (Figure 1). All exclusions will be recorded and reported. Patients who consent to participate will be invited for a consultation when they sign a written informed consent form and will be assigned a sequential study number.

**Figure 1. F1:**
[figure not shown]
Flowchart of the study protocol. mHHS: modified Harris Hip Score; mo: months; SF-12: 12-Item Short Form Health Survey; wk: weeks; y: years; *: clinical evaluator; **: surgeon; ***: radiographic evaluator; ****: data curator (supervisor).

Standard digital anteroposterior pelvis radiographs with calibration spheres will be obtained. A clinical interview and thorough preoperative evaluation will be undertaken by a medical doctor (orthopedic surgery resident). Functional, pain, and QoL questionnaires will be administered at this point, and surgical appointments will be scheduled (Multimedia Appendix 1).

Patient assignment and preoperative evaluations will be conducted in monthly blocks of 12 patients for practical and logistic purposes. Random allocation of patients to each group, the HG and the UG, will be performed at this time using double blinding.

At this stage, the surgeon will be blinded to group allocation and clinical assessment and will perform surgical planning for both uncemented and hybrid procedures using Peekmed software (Peekmed Inc, Braga, Portugal). Peekmed is a highly sensitive tool currently in use that focuses on digital surgical planning to evaluate the accuracy of corrections and to reproduce patient-specific anatomy. Data from both surgical plans will be extracted by the same surgeon using a specially designed digital form (MultimediaAppendices 2  3). Reports of the surgical plans will be printed and kept until surgery; however, only the correct plan, as decided by the random group allocation, will be provided to the surgeon by the assistant researcher before surgery.

### Inclusion and Exclusion Criteria

The inclusion and exclusion criteria are shown in Textbox 1.

Textbox 1.Inclusion and exclusion criteria.
**Inclusion criteria**
Age between 40 and 80 yearsClinical and radiographic diagnosis of hip arthritis (primary or secondary), unilateral or bilateralBoth sexes
**Exclusion criteria**
History of pathological fractures or active, uncontrolled metabolic and/or rheumatic diseasesSevere hip deformities with extensive acetabular defects, such as severe hip dysplasiaPrevious hip infection

### Withdrawal From the Study

Participants who wish to withdraw after the operation, as instructed in the preparticipation recommendations, may continue with usual treatment at the hospital. In the case of withdrawal at any point after surgery, the data will be considered missing, and data imputation techniques will be evaluated. Data from participants who discontinue the study will remain available in the electronic dataset during revision and will be presented in the results. The study will follow the Consolidated Standards of Reporting Trials (CONSORT) flow chart and tables.

### Randomization

Participants will be randomized and allocated to 2 different groups. On the day the participant signs the written consent form, each participant will receive a unique identification number that will be randomized later. Randomization will be performed in 10 random blocks of 12 participants each using Randomized.org. A computer-generated list will assign participants to either (i) the HG or (ii) the UG. An assistant researcher who is not involved in other study roles will carry out this allocation process. Data related to the randomization list will be kept confidential by the researcher in charge of the randomization. Consequently, both the researcher responsible for outcome evaluations and the participants will be blinded to group allocation.

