### Sample Size

The sample size was calculated using the Statulator Sample Size Calculation tool [25]. To disprove the null hypothesis of equality, assuming a pooled SD of 10.5 units for the HHS [6], the study would require a sample size of 60 participants per each group (ie, a total sample size of 120 for equal group sizes) to achieve a power of 80% and a significance level of .05 (2-sided) for detecting a true difference in means of 5.39 units between the test and the reference groups (ie, 56.9 vs 62.3).

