### Statistical Analysis

Results will be presented descriptively, with continuous data expressed as means (SD) and medians, and categorical data will be presented as means or percentages. For inferential analysis, the normality of the variables will be assessed using the Kolmogorov-Smirnov test. Dichotomous variables will be analyzed using the Fisher exact test and chi-square test, and continuous variables will be analyzed using the *t* test. Demographic data will be analyzed using ANOVA test, and the chi-square test will be used for the categorical data. In cases of non-normal distribution, appropriate nonparametric tests will be used according to the nature of the variable.

Primary outcomes, complications, and reoperations will be analyzed at 48 weeks. Paired and subgroup analyses are foreseen between periods of 3, 6, 24, and 48 weeks for the described outcomes. Results will be reported with 95% CI.

All statistical tests will be 2-sided, with a significance level of *P*=.05. Data will be analyzed using the Online Statistics Calculator, DATAtab/Numiqo (2025) [26]. Data from participants who receive additional treatments (eg, revision surgery for fractures) during study participation will be retained for intention-to-treat analysis.

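### Allocation runs in ten monthly blocks of 12, but the planned t test ignores the blocks: valid, slightly conservative if outcomes vary between months, and almost free to improve

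*Protocol article*

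**What the plan says.** All of this comes from the protocol article; no separate analysis plan is at hand.

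- **Randomization:** "Randomization will be performed in 10 random blocks of 12 participants each using Randomized.org".
- **Recruitment and Preoperative Assessment** (text after Figure 1): "Patient assignment and preoperative evaluations will be conducted in monthly blocks of 12 patients for practical and logistic purposes". The next sentence places random allocation at the same point, so the blocks are calendar cohorts and not only a device on the allocation list.
- **Study Design and Setting:** "A total of 120 patients will be enrolled in this study and randomly allocated to each group in a 1:1 ratio". The split within a block is not printed.
- **Statistical Analysis:** "continuous variables will be analyzed using the *t* test", with nonparametric tests as the fallback for non-normal data. No block, period or other covariate term is named.
- **Sample Size:** a plain two-group comparison of means, "assuming a pooled SD of 10.5 units for the HHS", for "detecting a true difference in means of 5.39 units between the test and the reference groups", with 80% power at two-sided 0.05, giving 60 per group.

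The Results section reports 72 patients enrolled and operated on by April 2025. That is 72 / 12 = 6 blocks, consistent with the monthly scheme.

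**The concern.** Balancing the arms within each month removes differences between months from the estimated treatment effect. An analysis that does not know about the months still counts those differences as random error. The reported standard error is then larger than the true one, confidence intervals are wider than they need be, and the real type I error lies below 5%.

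Some between-month variation is conceivable here. Patients come off a waiting list in some order, several doctors act as clinical evaluators, and part of the Harris Hip Score (HHS) is assessed by a physician. The sample size has no slack: 60 per group are required and 60 per group are planned. A needlessly wide interval is therefore unwelcome in a trial meant to say which construct is preferable, if either is.

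**Working it through.** **1. The plan's own figure.** Inputs from Sample Size: difference 5.39, SD 10.5, two-sided 0.05, power 80%.

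n per group = 2 × (1.960 + 0.842)² × 10.5² / 5.39² = 2 × 7.849 × 110.25 / 29.05 = 59.6, rounded up to 60. The stated figure reproduces. With 60 per group the standard error is 10.5 × √(2/60) = 1.917. Power is 80.3% by the normal approximation and 79.6% by the noncentral t.

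**2. The mechanism.** Let ρ be the share of HHS variance that lies between blocks. With 6:6 in every block the block effects cancel, so the true variance of the arm difference is (2/60) × SD² × (1 − ρ). The t test estimates about (2/60) × SD². Its standard error is therefore too large by a factor of about 1/√(1 − ρ).

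**3. What ρ means in HHS points.** For a straight-line drift over ten equally spaced blocks, the block positions 0 to 9 have SD 2.872. The change from first to last block is 10.5 × √ρ × 9 / 2.872. This gives 4.7 points at ρ = 0.02, 7.4 at 0.05, 10.4 at 0.10 and 14.7 at 0.20.

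**4. Simulation.** Ten blocks of 12 split 6:6, linear drift, 50,000 trials per scenario. The t test has 118 df and the model with block effects 109 df. Simulation error on a power near 80% is about √(0.8 × 0.2 / 50,000) = 0.2 points. The SE-ratio and type I error columns are for an overall SD of 10.5.

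| ρ (assumed) | SE ratio: formula / simulated | t-test type I error | Power, t test vs block model, if 10.5 is the overall SD | Power, t test vs block model, if 10.5 is the within-block SD and drift adds to it |
|---|---|---|---|---|
| 0 | 1.000 / 0.992 | 5.0% | 79.5% vs 79.5% | same |
| 0.02 | 1.010 / 1.010 | 4.8% | 79.9% vs 80.4% | 78.8% vs 79.3% |
| 0.05 | 1.026 / 1.022 | 4.5% | 80.4% vs 81.7% | 78.4% vs 79.9% |
| 0.10 | 1.054 / 1.046 | 3.9% | 80.5% vs 83.5% | 76.3% vs 79.5% |
| 0.20 | 1.118 / 1.119 | 2.8% | 82.4% vs 87.8% | 72.1% vs 79.4% |

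Random block effects instead of a linear drift give nearly the same picture. With overall SD 10.5, power is 80.5% vs 81.8% at ρ = 0.05 and 81.4% vs 83.9% at ρ = 0.10. The block model's type I error stays at about 5% throughout.

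**5. Hand check of the last column at ρ = 0.10.** The overall SD is 10.5 / √0.90 = 11.07, so the t test's standard error is 11.07 × √(2/60) = 2.021 and it rejects beyond 1.980 × 2.021 = 4.00. The true standard error is still 1.917. Power is about Φ((5.39 − 4.00) / 1.917) = Φ(0.72) = 76–77%, in line with the simulated 76.3%.

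**6. Interval width, overall SD 10.5.** The t test's half-width is 1.980 × 1.917 = 3.80 points. The block model's is 1.982 × 1.917 × √(1 − ρ): 3.76 at ρ = 0.02, 3.70 at 0.05 and 3.60 at 0.10.

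**7. Price of the block term with no drift.** By the noncentral t, power is 79.64% with 118 df and 79.58% with 109 df.

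**The case against.** The strongest reply is that nothing in the article shows any drift, and with none nothing is lost. The Level of Pragmatism table says the technique has been usual at the hospital for ten years, that the team and operating rooms are those of routine care, and that the waiting list at the start already held the whole projected population. The evaluators were engaged solely for this task and no turnover is described. The monthly blocks are explained by logistics, not by prognosis. This stands: drift is possible, not documented, and every magnitude here is conditional on an assumed ρ.

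The large scenarios are also hard to credit. A ρ of 0.20 needs a linear drift of 14.7 points, about 2.7 times the 5.39-point target, or month means scattering with an SD of 10.5 × √0.20 = 4.7 points. With one surgeon, one approach and one hospital that is unlikely.

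A reader might infer that the trial forfeits power its design had already secured. The article does not support that. Its sample size is a plain two-sample calculation that claimed no gain from blocking. If 10.5 is the overall SD, the t test's power stays at or slightly above its no-drift value. What is forgone is an extra, not part of the plan.

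It may also be said that model terms belong in an analysis plan that is not shown. That holds only in part, because the article does name the test. If a fuller plan contains a block term, the two texts need aligning.

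Finally, 6:6 per block is inferred, and withdrawals (Withdrawal From the Study) may leave it only approximate at 48 weeks. The cancellation is then approximate too.

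**Conclusion.** The point holds as a low-severity improvement to a stated method. The randomisation is blocked by month and the named analysis is not. If outcomes vary between months, the t test is valid but conservative.

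The likely size is small: at ρ of 0.02–0.05, a standard error 1–2% too large and about 0.5–1.5 power points forgone; at 0.10, about 5% and 2.5–3 points. Power falls below the planned 80% by more than rounding only if drift comes on top of the SD of 10.5. The article takes that SD from a cited study and does not say whether it includes such drift.

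Ignoring the blocks might be read as an invalid test or an inflated type I error. The direction is the opposite: the error rate is at or below 5% and the arm difference is not biased.

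The conclusion rests on 6:6 allocation per block, blocks that follow calendar months as described, and an assumed ρ.

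**What to change.** In Statistical Analysis, replace the t test for the 48-week HHS and the other continuous between-arm outcomes with a linear model containing treatment and randomisation block (ten levels, as a fixed factor or a random intercept). Report the arm difference and its 95% CI from that model. State in Randomization that each block of 12 is split 6:6, if that is so.

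The cost is one line of wording and at most 9 degrees of freedom (118 to 109), which moves the critical t from 1.980 to 1.982. Block number can be read from the allocation list, so no extra data are needed. The analysis of November 2025 described under Results does not list the 48-week HHS, so the model can still be fixed before that comparison. For radiographic outcomes already examined then, the date of the change should be declared.
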